### Design

This study uses a mixed methods triangulation design [19] that combines the collection and analysis of quantitative data on the process, context, and output (nurse–physician collaboration, medical delivery) of the intervention implementation with concurrent qualitative in-depth inquiries of the implementation procedures and context-bound influences. Data for the quantitative part will be repeatedly collected alongside the trial in all trial clusters by means of questionnaires, standardized interviews, and minutes targeting all parties involved in the intervention package implementation and/or the medical care for NHRs. The qualitative data collection will be conducted in a subsample of eight nursing homes and mainly focuses on the interaction between involved health professionals and their working processes. Data will be collected by a combination of non-participating observations and semistructured interviews conducted at different measurement points throughout the trial (Table 1).

**Table 1 Tab1:** Overview of data sources and measuring points by target groups for process evaluation (quantitative/qualitative)

Target population	Data collection	Measurement points							Target population and recruitment strategies	Sample size
		T0a	T0b	First training (only in IG)	Kick-off meeting (only in IG)	Second training (only in IG)	T1	T2		
*General practitioners (both study groups)*	Quantitative	x (Q)			x^a^ (Q)			x (Q)	All GPs involved in the medical care for participating NHRs and interested in participation For recruitment: • GPs will be invited in written form to take part in the *interprof* ACT trial, including. the process evaluation • All GPs will receive an expense allowance.	Data from a previous trial conducted in the German long-term care setting suggest a resident-to-physician ratio of approximately 3. A total number of about 210 GPs to be invited to participate in the process evaluation will be expected [8]. Based on previous data, a response rate of 45% is assumed, reducing the sample size to about 95 GPs [20–22].
	Qualitative		x (I, O)		x (O)		x (I, O)	x (I, O)	GPs who participate in the main trial and agree to participate in the process evaluation. For recruitment: GPs will be contacted in writing and/or via telephone by members of the research team.	On average, two GPs per NH per measurement point are expected. Participation at each kick-off meeting (*n* = 5) of the subsample of the qualitative process evaluation will be expected.

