*Registered nurses (both study groups)*	Quantitative	x (Q)			x^a^ (Q)			x (Q)	All RNs working in direct nursing and medical care for the NHRs throughout the day, evening, or night shifts at data collection days. For recruitment: RNs will be contacted in writing and orally by study team members involved in data collection for main trial outcomes.	On average four RNs may be reached per cluster, representing approximately 30% of the target population [8].
	Qualitative		x (I, O)		x (O)		x (I, O)	x (I, O)	RNs pre-selected by nursing or facility directors based on their involvement in interprofessional collaboration. RNs are included if they are available and willing to take part in the qualitative process evaluation. For recruitment: RNs will be contacted in writing and/or via telephone by members of the research team.	On average, two RNs per NH per measurement point will be expected. Participation at each kick-off meeting (*n* = 5) of the subsample of the qualitative process evaluation will be expected.
*Nursing home residents (both study groups)*	Quantitative	x^b^ (Q)			x^a^ (Q)			x^b^ (Q)	All NHRs participating in the *interprof* ACT trial, i.e., meeting following inclusion criteria [12]: • Have experienced at least one GP contact in the last three months or two GP contacts in the last 6 months or were admitted to the nursing home during the preceding 6 months independently of the actual number of documented GP contacts • Are aged 18 years or older • Provide written informed consent for the study, either by themselves or through their legal guardian Of these, only NHRs able to answer simple questions of satisfaction with medical care by themselves are to be included in the process evaluation. For recruitment: Detailed recruitment strategies and methods to appraise NHRs’ ability to answer questions are described in the main trial protocol [12].	As estimated for the *interprof* ACT trial [12].
	Qualitative				x (O)				NHRs who are co-subject of non-participating observations. For recruitment: In these cases, NHRs will be informed about the observation in written and oral form before the observation takes place. NHRs or their legal guardian must provide informed consent.	Not applicable

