### Data management

Study data in the process evaluation will be recorded both pseudonymized (Nursing or facility directors, NHRs) and anonymized (RNs, GPs, IPAVS, and study team members). For pseudonymized data, the personal data of the study participants will be kept separately from the study data. A retrospective correlation to a person is only possible with the help of a “key” which is maintained in the study center. The data will be entered into the electronic database according to the four-eye principle. The paper-based data is stored in the participating study centers and electronically in the database on a server. To ensure data quality, a plausibility check of the data will be carried out by an independent monitor. All original data will be stored for 10 years and destroyed afterwards. Generally, all data will be handled according to current data protection law.

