Initially, all quantitative data will be analyzed and aggregated at the cluster (i.e., nursing home) level. For this aggregation, a two-step approach will be used. First, the direction and size of changes over time will be descriptively estimated for single items or subscales. For the assessment of pre-post changes (T0 versus T2), the difference between the two mean or median values will be estimated. Following the effect size Cohen’s *d* [44], a mean difference with a size of ≥20% of the standard deviation across study groups will be interpreted as a relevant change or difference. For median values, a median difference of 0.5 in case of ≤5-step scales or 1.0 in case of >5-step scales will be regarded as relevant. Change estimates will be classified as follows: relevant changes in the favorable direction reflect positive changes, relevant changes in the nonfavorable direction reflect negative changes, and nonrelevant changes are interpreted as indifferent effects (no changes). Some items will be assessed only at the T2 follow-up visit to directly measure the subjectively perceived degree of change in certain collaboration or care procedures. For these items, the size of the change will be classified based on the distance between the estimated mean value and the most neutral value of the scale. If the mean value is higher (positive values) or lower (negative values), the distance between 20% of the pooled standard deviation and the most scale-neutral value, a relevant change will be assumed, either positive or negative, depending on the direction. In other cases, the mean values will be regarded as being indifferent.

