Second, the change estimates across items and subscales will be aggregated by means of vote counting, i.e., the number of positive and negative changes and indifferent findings will be counted and visually depicted in tables for single-outcome subdomains or dimensions. Vote counting findings from each perspective (NHRs, NHDs, RNs, IPAVs, GPs) will be summarized per nursing home in tables (intervention group only), and nursing homes will then be ranked with regard to their degree of implementation achieved for each *interprof* ACT component. Based on this ranking, nursing homes will be inspected for differences in contextual factors. These findings will then inform the triangulation of qualitative and quantitative data and the subsequent creation of a preliminary model to answer the second research question, i.e., the impact of the degree of implementation on the quality of interprofessional collaboration, taking moderating effects of potentially relevant contextual factors into account.

Furthermore, for the outcome domains “implementation of the *interprof* ACT intervention package,” “key elements of interprofessional collaboration,” and “further domains related to interprofessional collaboration and medical care,” the vote counting findings per nursing home will be visually compared between the intervention and control groups to explore between-group differences in the changes in attitudes and current practice and the quality of RN-GP collaboration.

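### For a single RN or GP item, the 0.2 SD relevance rule is applied per nursing home to about four RNs or three GPs, so with no true change roughly 8 in 10 homes would be labelled positive or negative

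*Protocol article*

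**What the plan says.** Under Data analysis, Quantitative data, the protocol article states that initially "all quantitative data will be analyzed and aggregated at the cluster (i.e., nursing home) level". In the first step, "the direction and size of changes over time will be descriptively estimated for single items or subscales". For pre-post comparisons of means, "a mean difference with a size of ≥20% of the standard deviation across study groups will be interpreted as a relevant change or difference". Differences that reach the threshold are classed as positive or negative by direction; of the rest it says "nonrelevant changes are interpreted as indifferent effects (no changes". Medians have a separate cut-off: 0.5 on scales of up to five steps and 1.0 on longer ones.

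In the second step, "the number of positive and negative changes and indifferent findings will be counted and visually depicted in tables". The counts are summarized per home and perspective, intervention homes are ranked on implementation of each component, and ranked homes are inspected for contextual differences. The counts per home are also compared visually between study groups. Under Triangulation, the findings go into joint displays that guide a data-driven choice of variables for the regression.

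Table 1 gives the expected respondents. For RNs: "On average four RNs may be reached per cluster, representing approximately 30% of the target population". For GPs, about 210 are invited and "a response rate of 45% is assumed, reducing the sample size to about 95 GPs". The Data management section lists as "anonymized (RNs, GPs, IPAVS, and study team members" the groups whose data cannot be traced to a person.

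**The concern.** A cut-off of 0.2 SD is a reasonable convention for a difference that is well estimated. Here it is applied to the difference between two means of three or four people each, with no interval, no minimum number of respondents and no category for differences too imprecise to judge. If sampling error is several times the threshold, most labels on an unchanged item will be positive or negative by chance, and a home that truly improved can readily be labelled worsened. The remaining label also misleads: a small difference between two very small samples is not evidence that nothing changed. At stake is how much of the per-home tables, and of what is drawn from them, is signal.

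**Working it through.** **Inputs.** Threshold 0.2 SD (Quantitative data). RNs per home: 4 (Table 1). GPs: 210 × 0.45 = 94.5, which reproduces the stated figure of about 95; over 34 homes, 95/34 = 2.8 per home (derived, not stated). RN and GP answers are anonymized, and RNs are those working on the collection days, so the base case treats T0 and T2 as independent samples. SD is read as the respondent-level SD.

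**Standard error of one home's change.** SE = SD × √(2/n).
- RNs: √(2/4) = 0.71 SD.
- GPs: √(2/2.8) = 0.85 SD.

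**Label rate with no true change.** P = 2 × [1 − Φ(0.2/SE)].
- RNs: 0.2/0.707 = 0.283, P = 0.78 (about 39% positive, 39% negative).
- GPs: 0.2/0.846 = 0.236, P = 0.81 (about 41% each way).

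**With a true benefit.** P(positive) = Φ((d − 0.2)/SE) and P(negative) = Φ((−0.2 − d)/SE).
- RNs, d = 0.3 SD: positive Φ(0.141) = 0.56, negative Φ(−0.707) = 0.24, indifferent 0.20.
- d = 0.5 SD: negative 0.16 (RNs) and 0.20 (GPs).

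**Sensitivity with no true change.** Correlation, ICC and the population correction are assumptions; the document gives none of them.

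| Assumption | RNs | GPs |
|---|---|---|
| Base case | 0.78 | 0.81 |
| Finite-population correction, SE × √(1 − f), f = 0.30 / 0.45 | 0.74 | 0.75 |
| T0–T2 correlation 0.5, SE = √(2(1 − 0.5)/n) | 0.69 | 0.74 |
| Correlation 0.7 and ICC 0.1, SE = √(0.9 × 2 × 0.3/n) | 0.59 | 0.65 |

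If SD meant the SD of home means, the RN rate would rise to 0.84–0.88 (ICC 0.2 to 0.05).

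**Other rules and respondents.**
- Median rule: simulated five-point items under three assumed answer distributions gave 54–64% at n = 3 and 71–77% at n = 4. The mean rule on the same items gave 83–87%.
- Residents: if 210 × 3/34 = 18.5 per home answered, SE = √(2/18.5) = 0.33 SD and P = 0.54. This is an assumption and an upper one, since only residents able to answer take part.

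**Study-group level.** About 4 × 17 = 68 RNs and 95/2 ≈ 47 GPs per group give SE = √(2/68) = 0.17 SD and √(2/47) = 0.21 SD before any allowance for clustering. The threshold is of the same order as the SE here, so an interval is still needed.

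**The case against.** The strongest reply is that the plan calls all analyses explorative, describes the changes as descriptive estimates and made no formal sample size calculation. The labels stand beside qualitative data and an a priori logic model, the final regression adjusts for cluster effects, and no trial endpoint depends on them. That lowers the severity. It does not make the labels informative, and the plan does use them to rank homes and choose variables.

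Other points also stand. Anonymity prevents linking but does not make the samples independent; overlapping respondents lower the SE, as the sensitivity table shows. Part B forms can give more than four RN ratings per home, although these are clustered within raters.

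Several stronger readings are tempting but unsupported:
- A reader might infer that 8 in 10 homes would be declared improved or worsened overall. The label attaches to one item or subscale from one perspective, not to the home.
- A reader might infer that everything downstream mostly reflects who was on shift. Five perspectives contribute, and only RNs are sampled by shift. Sampling error does not apply in the same way to directors and IPAVs, and IPAV 10-step ratings measure dose and reach directly.
- A reader might infer that the rule ruins the ranking or the group comparison. With no change, false labels split evenly; at 0.3 SD the split is 56 to 24, so direction is partly preserved over 17 homes per group. In simulation with an assumed between-home SD of change of 0.3 SD, ranking by votes and by mean change agreed similarly with the truth (rank correlation about 0.45–0.49). The weak ranking comes from few respondents, not from the rule itself.

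**Conclusion.** The concern holds for RN and GP items and subscales judged by the mean rule within single homes. With no true change, about 78% (RNs) or 81% (GPs) of homes would be labelled positive or negative on a given item. This rests on independent T0 and T2 samples, the respondent-level SD, approximately normal means and 2.8 GPs per home; GPs serving several homes would raise that number somewhat. Strong respondent overlap or a finite-population correction brings the rate to about 6 to 7.5 in 10, which does not rescue the rule. It is lower for residents, and for the median rule at n = 3. The labels therefore carry much sampling noise into the vote counts, ranking, group comparison and variable selection. The plan should be changed, but given its explorative status this is not a critical fault.

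**What to change.** For RN and GP data, stop converting single-home differences into positive, negative or no-change labels. Report each home's change as a continuous estimate with the number of respondents and an interval, preferably partially pooled from a mixed model with home and respondent effects. Use these estimates for the ranking and the joint displays, and do not read a small or imprecise difference as no change. Apply the 0.2 SD rule to study-group mean changes, with confidence intervals that allow for clustering.

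Do not replace the rule with a home-level label that requires the interval to exclude zero. With n = 4 and a between-home SD of change τ of 0.2–0.5 SD (assumed), a shrunken 95% interval excludes zero only if the raw change exceeds 1.96 × √0.5 × √(τ² + 0.5)/τ. That is 5.1 SD at τ = 0.2 and 2.4 SD at τ = 0.5, so with zero mean change fewer than 1% of home-items would be labelled.

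The cost is revised analysis wording and modest programming, with no new data; the article reports that analysis is still ongoing. The drawback is that the per-home tables will look less decisive. Pooling will not recover much home-level information either: the reliability τ²/(τ² + 0.5) of one RN item's change is only 0.07–0.33 over the same range.

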## Methods

### Aims

The overall aims are to assess the change in RN-GP collaboration induced by the implementation of the *interprof* ACT intervention package and to identify contextual determinants of implementation success and its downstream effects on intermediate outcomes. Following existing frameworks for process evaluations of complex interventions [16, 17], this overall aim is divided into several sub-objectives, each focusing on one specific part of the assumed causal pathway from group allocation to the impact of the interventions on the intermediate outcomes (i.e., the interprofessional collaboration). To capture the whole picture, the process evaluation comprises a quantitative part and a qualitative part. The main objective of the quantitative part is to estimate the degree of implementation of the *interprof* ACT components and its downstream effects on the quality of the RN-GP collaboration. Therefore, it addresses the following research questions:What is the degree of implementation of the *interprof* ACT components with regard to dose and reach, fidelity, and local adaptations? To what degree does this implementation output vary between clusters?What are the effects of the implementation of *interprof* ACT components on the quality of RN-GP collaboration?Which contextual factors at the system, organization, intervention, staff, and NHR levels influence the implementation of the *interprof* ACT components as well as the quality of RN-GP collaboration?

The qualitative part mainly aims to assess the *interprof* ACT intervention with regard to feasibility and prospects for successive implementation into routine care. Therefore, it mainly addresses the following research questions:How do relevant working processes change as a result of the implementation of *interprof* ACT intervention package?How can effective processes be described and defined in a standardized form (process map)?

Altogether, the results of the process evaluation will facilitate the understanding of causal mechanisms behind the main trial findings and point to important facilitators and barriers as well as preferred strategies for large-scale implementation of the *interprof* ACT intervention package in routine care given that the trial results will be in favor of the intervention.

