The major outcome domain “implementation of the *interprof* ACT intervention package” contains several domains and subdomains to measure the success of the implementation activities in terms of the following dimensions: dose and reach of the intervention package as a whole and of the individual *interprof* ACT interventions, adaptations made to the single interventions, and attitudes and subjectively experienced quality with regard to these interventions. Adaptations made to the *interprof* ACT interventions will be recorded by study team members by completing semistructured minutes of the kick-off meetings and the supervision encounters as well as by IPAVs (questionnaires at T1 and T2). Dose and reach are directly measured by repeated 10-step global judgments of the IPAVs on the degree of implementation (1 = not implemented, 10 = fully implemented). The judgments of IPAVs, RNs, nursing home directors, GPs, and NHRs on attitudes, current practices and/or subjectively experienced quality of/satisfaction regarding *interprof* ACT interventions will provide an indication of the fidelity and quality of the implementation. Respective judgments will be collected at T0 and T2 by means of standardized questionnaires comprising self-developed items and items of existing measurement instruments with established psychometric performance [26, 28–31] (Table 2 and Additional file 2).

Two other major domains, “key elements of interprofessional collaboration” and “further domains related to interprofessional collaboration and medical care,” address the key elements of interprofessional collaboration (e.g., interprofessional communication, involvement of NHRs, contribution of involved professions), additional aspects of collaboration and experiences of quality of care assumed to be influenced by the *interprof* ACT intervention package (Fig. 3). These outcomes will be assessed in terms of attitudes, current practice, and subjectively experienced quality or satisfaction from various perspectives (IPAVs, RNs, nursing home directors, GPs, and NHRs) at different measurement points (T0, T2). Standardized questionnaires consisting of self-developed items and items of established measurement tools [25–28, 31–33] will be used (Table 2 and Additional file 2).

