#### Triangulation

In addition to the separate analyses of quantitative and qualitative data, synthesis and joint analysis of quantitative and qualitative findings are planned to enhance the quality of the process evaluation and to evaluate and adapt the underlying logic model in accordance with the empirical findings. Concretely, triangulation will allow us to explore the impact of the degree and fidelity of the implementation of the *interprof* ACT intervention package on the quality of interprofessional collaboration, the interaction between contextual factors and the success of implementation, and the quality of interprofessional collaboration.

For this purpose, quantitative and qualitative findings will be integrated at different timepoints. First, after collecting initial T0 data sets, preliminary qualitative insights regarding the determinants of interprofessional collaboration and contextual factors will be exchanged and discussed against preliminary experiences derived from the supervision of IPAVs to allow for the adjustment of subsequent T1 and T2 questionnaires for emerging themes.

Second, after completion of the T2 data collection, the findings of the separate quantitative and qualitative analyses will be systematically cross-mapped in “joint displays” to compare and contrast insights. This procedure allows us to consider detailed variations within and across clusters (i.e., nursing homes) regarding implementation success, the quality of RN-GP collaboration, and potentially relevant contextual factors. In particular, this step enables a data-driven selection of variables for a model that, based on the a priori logic model, depicts the associations between these variables. To assess the direction and size of the impact of the implementation success on important variables of RN-GP collaboration, this model will be subject to generalized linear regression analyses. These analyses will both adjust for cluster-related effects and account for moderating effects of potentially relevant contextual factors. The exact regression model will be chosen based on the actual size and characteristics of available data. By ensuring that quantitative and qualitative analyses build upon each other [17], this triangulation facilitates the creation of a theoretically and empirically informed model for the final statistical exploration of core associations of assumed causal pathways of the *interprof* ACT intervention package.

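### The randomised groups are compared on RN-GP collaboration only by eye, on vote counts; an estimate by allocated group with an interval should be added

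*Protocol article*

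**What the plan says.** **Aim.** The Aims section opens: "The overall aims are to assess the change in RN-GP collaboration induced by the implementation of the" package. Research question 2 asks for the effects of implementing the components on the quality of collaboration.

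**Data.** Tables 1 and 2 show collaboration domains collected in both study groups at T0a (before randomisation) and T2, mainly from RNs, GPs and nursing home directors, with residents on some domains.

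**Comparison of the groups.** Under Quantitative data, the change in each item or subscale is classed per home as positive, negative or indifferent, with a threshold of 20% of the SD when means are used. The classes are counted within subdomains, and then "the vote counting findings per nursing home will be visually compared between the intervention and control groups". The stated purpose is to explore differences between the groups.

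**Formal model.** Under Triangulation: "To assess the direction and size of the impact of the implementation success on important variables of RN-GP collaboration", a generalized linear regression is planned, with adjustment for clustering and for moderating contextual factors. Of its variables the section says that "this step enables a data-driven selection of variables for a model", and of its form: "The exact regression model will be chosen based on the actual size and characteristics of available data".

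**Measure of implementation.** Data collection methods states: "Dose and reach are directly measured by repeated 10-step global judgments of the IPAVs". IPAVs exist only in intervention homes. Other respondents in both groups report on attitudes, current practice and quality for the components.

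**Status.** Data analysis declares all analyses explorative, and no formal sample size was estimated.

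**The concern.** The aim is worded causally, and the design has what is needed to address it: 34 randomised homes measured before and after with shared instruments. The plan does not turn the randomised contrast into an estimate. Changes in home means are reduced to three categories and the groups are then judged by eye. A reader of the results could not say how large a difference is or whether chance explains it.

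The one model that yields an effect size depends on how well homes implemented the package. That is decided after randomisation and is open to confounding. The Discussion itself reports that, in an earlier trial of a similar intervention, implementation success was driven largely by the homes' own motivation. Motivation could plausibly also affect collaboration.

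**Working it through.** **Inputs from the article.** 34 homes, 17 of them in the intervention group; about four RNs reached per home; about 210 GPs invited with 45% response; vote threshold 0.2 SD; RN and GP data anonymised (Data management), so T0 and T2 answers cannot be paired by person as described.

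**Assumed, because not stated.** Two-sided alpha 0.05; ICC as given in each step; correlation of true home effects between waves 0.5 to 1.0; normal scores with SD 1.

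**The article's own figure.** 210 × 0.45 = 94.5, which agrees with its figure of about 95 GPs. Per home, 95/34 = 2.8.

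**1. Votes when nothing has changed.** With m = 4 independent RNs per wave, respondent SD 1 and stable home effects, the T2 − T0 difference in a home's mean has SE = √(2/4) = 0.707 SD. P(positive) = 1 − Φ(0.2/0.707) = 0.389, and P(negative) is the same. About 78% of home-by-item results would therefore be classed as relevant change. If the waves correlated 0.8 the figure would still be 53%.

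**2. Gap between groups on one item.** The SE of the difference in the share of positive homes is √(2 × 0.389 × 0.611/17) = 0.167. The exact binomial probability of a gap of 20 percentage points or more, in either direction, is 0.217. This describes a single item. The planned display counts several items per home, but the same few respondents answer them, so their errors are not independent.

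**3. Information lost.** Simulation with a true effect of 0.5 SD, 17 v 17 homes and four RNs per wave (20,000 runs per setting, ICC 0.05 to 0.20):

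| Analysis of the same data | Power |
|---|---|
| t test on votes (+1, 0, −1) | about 35 to 49% |
| t test on home change scores | about 45 to 60% |
| home-level ANCOVA, T2 mean on group and T0 mean | about 62 to 75% |

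In these runs about 65 to 68% of intervention homes voted positive and 13 to 18% negative. In controls about 38 to 40% voted positive.

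**4. Precision available.** The variance of a home mean is ICC + (1 − ICC)/m, and the SE of the group difference is √(2 × variance/17). For RNs (m = 4, ICC 0.1) this is √(2 × 0.325/17) = 0.196 SD. With t on 32 df the 95% half-width is 0.40 SD.

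| | ICC 0.01 | ICC 0.30 |
|---|---|---|
| RN (m = 4), half-width | 0.35 SD | 0.48 SD |
| GP (m = 2.8), half-width | 0.42 SD | 0.52 SD |

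If baseline home means correlated 0.5 with T2, these would fall to 0.31 to 0.42 SD (RN) and 0.36 to 0.45 SD (GP). That correlation is optimistic at low ICC.

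**5. The regression on implementation success.** Simulation of 17 homes with no true effect and one unmeasured confounder equally correlated with implementation and collaboration:

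| Correlation with each | Mean r | p < 0.05 |
|---|---|---|
| 0.3 | 0.09 | 6% |
| 0.5 | 0.24 | 16% |
| 0.7 | 0.48 | 54% |

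This illustrates an analysis based on the IPAV ratings, which exist only in the intervention group. It does not reconstruct the final model, whose form is left open.

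**The case against.** **The regression answers the question asked.** The Quantitative data section restates research question 2 as the impact of the degree of implementation on collaboration. That is a dose-response question and proper in a process evaluation. This stands: the group contrast serves the overall aim and should not displace that answer.

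**The work is exploratory.** This also stands, and it lowers the priority. It excuses the absence of a powered test but not of an estimate with an interval, since the plan already uses regression elsewhere.

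**A group term is not excluded.** The Design section speaks of models for the downstream effects of the intervention, and the form of the regression is open. True, but the exposure that Triangulation names is implementation success, and the method for comparing the groups is stated as visual.

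A reader might also infer more than the text supports:

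- *That the regression is confined to 17 homes.* The IPAV ratings and the implementation ranking are, but component practice is reported in both groups and Triangulation sets no such limit.
- *That baseline is ignored.* Most votes rest on T0 to T2 changes, so baseline is differenced out, though less efficiently than by covariance adjustment.
- *That all data are unlinked.* Resident and director data are pseudonymised with a key; the point applies to RNs and GPs.
- *That a group contrast would be free of bias.* RNs are those on shift on collection days, GP response is assumed to be 45%, and respondents who know the allocation report on their own practice. Randomising homes removes none of this.

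**Conclusion.** The point holds as a should-fix. The overall aim is causal and the data for a randomised contrast are collected, but the plan compares the groups by eye on a coarse and noisy summary. The only effect size it would report is for a non-randomised exposure.

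The 39% figure for false positive votes follows from four unlinked RNs per home and the 0.2 SD threshold. The power comparison and the achievable half-width of roughly 0.3 to 0.5 SD rest on the assumed ICC and wave correlations. Their exact values would move with those assumptions, but the ordering of the three analyses held in every setting run.

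A reader might conclude that research question 2 goes unanswered or that the process evaluation is invalid. The article supports neither. The regression addresses that question as defined, and no confirmatory claim is attached to the visual comparison.

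**What to change.** 1. Name in advance a small number of collaboration scores, by respondent group, for comparison by allocated group. Keeping the list short limits multiplicity.
2. For each, model the T2 score on allocated group, T0 home mean and study centre. Use a home-level ANCOVA, or a mixed model with a random effect for home where individual data are used (and for respondent where one person returns several part B forms), with small-sample degrees of freedom.
3. Report the difference with a 95% CI as exploratory estimation of the overall aim, and state the possible respondent selection and self-report bias.
4. Keep the vote-count displays as illustration.
5. Keep the implementation-success regression as the dose-response answer to research question 2, labelled observational.

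**Cost.** A few more models and some wording; no new data. Precision will be modest, so a wide interval must not be read as no effect. The article reports data collection finished and analysis ongoing. The scores should therefore be fixed before results by group are examined or, if that has already happened, the added analysis should be declared post hoc.
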